## Abstract

**Background:**

Fatigue in combination with gait and balance impairments can severely limit daily activities in people with multiple sclerosis (PWMS). Generalised fatigue has a major impact on walking ability, with moderately disabled PWMS experiencing difficulty in walking extended distances. Localised motor fatigue in the ankle dorsiflexors can lead to foot drop, further reducing functional ambulation. The aim of this study is to evaluate the effect of a simple dynamic dorsiflexion assist orthosis on walking-induced fatigue, gait, balance and functional mobility in PWMS.

**Methods:**

A randomised cross-over trial will be conducted with 40 community dwelling PWMS with mild to moderate mobility disability. Participants will initially be screened for disease severity, balance, strength, depression and fatigue at the South Australian Motion Analysis Centre. On two non-consecutive occasions, within two weeks, participants will undergo either the 6-minute walk test (6MWT) or the 6MWT while wearing a dorsiflexion ankle orthosis (with a randomised condition order). Distance walked, perceived exertion, perceived fatigue and the physiological cost of walking (the primary outcome measures) will be compared between the two walking conditions. Additional pre- and post-6MWT assessments for the two conditions will include tests of strength, reaction time, gait and balance.

**Discussion:**

This study will increase our understanding of motor fatigue on gait and balance control in PWMS and elucidate the effect of a Dynamic Ankle Orthosis on fatigue-related balance and gait in PWMS. It will also examine relationships between mobility and balance performance with perceived fatigue levels in this group.

**Trial Registration Number:**

ACTRN12612000218897

## Background

People with Multiple Sclerosis (PWMS) have difficulties with gait and balance that can significantly limit activities of daily living and may increase the risk of falls [1]. Disruption to central nervous system integration of proprioception, visual and vestibular sensory information are all likely to contribute to balance problems and fall risk in this population [1-3]. Perceived levels of fatigue are also associated with balance problems and falls in PWMS [4], while exercise-induced fatigue has been shown to reduce balance control in a backward leaning task [5].

Changes to gait can be detected early in the disease course, even in PWMS without any mobility limitations [6]. In fact, early gait and balance changes can be detected in PWMS who have no pyramidal signs or clinical disability [7]. These changes may be, in part, due to lower limb motor fatigue, which is commonly reported in PWMS and appears to worsen with increasing walking distance [8]. A previous study showed no significant kinematic variability in gait with fatigue in a mildly disabled group of PWMS [9]. However, fatigue related changes in gait variability may become apparent in PWMS with more severe disability levels. As with generalized fatigue in MS, our current understanding of motor fatigue is limited. Ankle dorsifexors are particularly susceptible to the effects of motor fatigue, with both central and peripheral neuromuscular alterations contributing to fatigue-related weakness [10].

In rehabilitation, treatments addressing dorsiflexion weakness during gait can include specific dorsiflexor exercise and/or prescription of an Ankle Foot Orthoses [11]. To date, studies have been unable to indicate the effectiveness of these orthoses in improving ambulation in PWMS [12]. Static and dynamic ankle foot orthoses have been shown to improve static balance, but impair dynamic balance when walking [13]. The Dorsiflexor Assist Orthosis (DAO) (Foot Up, Ossur©) differs from standard ankle orthoses as it dynamically assists the foot into dorsifexion with an elastic strap without affecting the sensory input of the foot inside the shoe.

Moderately disabled ambulatory PWMS who have mobility difficulties that impact on their ability to undertake daily activities often seek outpatient or community physiotherapy with the aim of improving or maintaining mobility levels, but unfortunately, there is limited evidence to inform clinicians with regard to best practice in this area. The aim of this study, therefore, is to evaluate the effect of a possible therapeutic device (i.e. a DAO) on the six-minute walk test (6MWT), walking efficiency and perceived levels of fatigue and exertion. The 6MWT was selected as the fatiguing condition as it has been evaluated in PWMS as a measure of functional capacity and because PWMS have reduced 6MWT distance when compared with controls [14]. In addition, we anticipate that in a moderately disabled group, the 6MWT will induce fatigue and changes to gait and balance control. We will therefore examine any deterioration in function by in gait patterns, balance and tests of motor function following walking the 6MWT with and without the DAO.

## Methods

### Design

A randomised cross-over trial will be conducted with 40 community-dwelling PWMS (Figure 1).

**Figure 1 F1:**
[figure not shown]
Randomised cross-over trial design.

### Participants

Participants will be recruited from the MS Society of South Australia, the multidisciplinary MS Clinic at Repatriation General Hospital (RGH) and from private physiotherapy clinics in South Australia. To be included, participants must: (i) have a definite diagnosis of MS; (ii) have mild to moderate difficulty in mobility with an Expanded Disability Status Scale (EDSS) score of 3.0-6.0; (iii) be able to walk for 6 minutes unaided or with the aid of a walking stick. Participants will be excluded if they: (i) have had an exacerbation or relapse of MS within the past 3 months; (ii) use medication prescribed for fatigue or mobility such as Amantadine, Modafinil or Fampridine; (iii) have significant cardiac or respiratory disease; (iv) suffer from severe depression, or (v) have arthritis, fibromyalgia or pain that severely limits walking. All participants will provide informed written consent prior to involvement in the study. The Repatriation General Hospital Research and Ethics Committee have approved the study protocol, registration number EC00191.

### Setting/location

Assessments will take place at the South Australian Movement Analysis Centre at the Repatriation General Hospital, Adelaide.

### Screening and initial assessments

Participants will initially be screened for disease severity with the EDSS by a certified Neurostatus investigator (http://www.neurostatus.net). Additional initial assessments will include: (i) tests of vision, strength, balance, reaction time and sensation [15]; (ii) measurements of height and weight to calculate Body Mass Index (BMI); (iii) the Fatigue Severity Scale (FSS) [16]; (iv) the Modified Fatigue Impact Scale (MFIS) [17,18]; (v) the Beck Depression Inventory –Fast Screen (BDI-FS) [19]; and (vi) the Multiple Sclerosis Walking Scale (MSWS-12) [20,21].

### The walking protocol and Pre- and post-walk assessments

Following initial screening and assessments, participants will be randomised with respect to condition order (i.e. 6MWT with or without DAO), and subsequently undertake the baseline pre-walk assessments. Immediately following the 6MWT, participants will undertake the post-walk assessments. The pre- and post-walk assessments include tests of strength, simple reaction time, choice stepping reaction time, standing balance, and gait analysis, as described below and presented in Figure 1. Participants will return to the laboratory within 2 weeks to complete the other 6MWT condition and associated pre- and post-walk assessments.

#### Walking protocol & perceived exertion

Participants will wear a Polar heart rate monitor during each walking condition. Participants will be seated at rest for 2 minutes to determine a baseline heart rate. We will use a modified 6MWT version from the American Thoracic Society script with the aim of maximising effort and inducing fatigue [15]. Participants will be instructed to walk back and forth along a ten-metre walkway as fast as possible over the six-minute testing period with the instructions “walk as fast as you comfortably can, bearing in mind that you will be walking for 6 minutes”. Participants will be permitted to use assistive devices (i.e. canes) if required. Distance walked and perceived exertion will be recorded each minute using the 10-point Modified Borg Rating of Perceived Exertion (RPE) scale [16], and heart rate (beats/min) will be automatically recorded at 5-second intervals. Physiological Cost Index of walking will be calculated by the formula;

(1)$$\left(\text{average 6MWT HR }–\text{ average resting HR}\right)/\text{ walk speed}\text{,}$$

where heart rate is measured in beats/min and walk speed measured in m/min [17].

#### Perceived fatigue levels

Participants will be asked to indicate their perceived fatigue levels will be measured using the Visual Analogue Scale for Fatigue (VAS-F) [18] immediately before and after the 6MWT.

#### 3D Gait analysis

3D gait analysis will be conducted using an 8 camera Vicon MX3 system (Vicon, Oxford, UK) with 4 AMTI (AMTI, Watertown, MA) force plates and Helen Hayes marker set [19]. Spatiotemporal data and kinematic and kinetic data for the hip knee and ankle will be collected over a minimum of 6 walking trials with and without the DAO. Data will be collected using Vicon Nexus software (v1.4) and processed with Matlab (v7.0). Sagittal plane angles at the ankle are of particular interest, to examine effects of the DAO, in addition to knee and hip angles to identify potential compensations for DAO effects at the ankle.

#### Strength

Knee extension and ankle dorsiflexion strength will be determined as isometric force (kg) produced, measured with a strain gauge linear to direction of force production, normalised to body mass. Strength tests will be conducted in a seated position. For knee strength testing, the hip and knee will be positioned in 90 degrees of flexion. The test of ankle strength will be conducted with the ankle at 30 degrees of plantarflexion. Each strength test will be repeated 3 times with sufficient rest in between, and the maximum score recorded [20].

#### Simple reaction time

Participants will be seated in a chair with ceiling lights dimmed. Simple reaction time will be measured in milliseconds using a handheld electronic timer, with participants seated and using a light as the stimulus and a finger-press (hand reaction time) or a foot-press (foot reaction time) as the response. Five practice trials will be followed by an additional 10 trials, for which reaction time in milliseconds will be recorded for each trial and averaged [20].

#### Choice stepping reaction time (CSRT)

The CSRT device consists of a floor-mounted mat that contains six plates (32 X 13 cm): two base plates on which the participant stands and four target plates. A computer monitor displays a corresponding image of the mat. One of the stepping plates on the computer image light up in a random order. The participant will be instructed to step on to the corresponding illuminated plate as quickly as possible, using their left foot for the targets to the left and to the front left, and their right for the targets to their right and front right. Reaction times for (i) time to lift the foot from the base plate and (ii) time to land the foot on target plate will be recorded. Each plate will be presented 5 times, and sufficient time will be given between each trial to re-establish balance and minimise fatigue [21,22].

#### Standing balance

Standing balance will be measured while participants stand on two AMTI force plates. Postural position of C7 and sacrum will be measured using reflective markers and an 8-camera Vicon© MX3 system. The participant will stand for 30 seconds under 4 conditions: (i) eyes open feet apart; (ii) eyes open feet together; (iii) eyes closed feet apart; and (iv) eyes closed feet together. Each condition will be repeated with the 8 trials presented in a randomized order.

### Primary outcome measures

The primary outcome measures are walking distance, physiological cost index and perceived fatigue and exertion during the 6MWT.

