### Sample size calculations

We used the “Inequality Tests for Two Means in a 2x2 Cross-Over Design using Differences” module from the Power Analysis and Sample Size (PASS) software [18] for estimating the sample size required for the primary outcome measure of 6MWT distance. The following parameters were entered into the calculation: power = 0.8; alpha = 0.05; N(total sample size) = 20,30,40; mean difference between groups at retest = .50,100,150. Standard deviation measures were estimated from previous studies [11]. The difference in 6MWT distance was based on the rationale that a clinically meaningful increase in metres walked by MS patients in this test is 100 m (i.e. the difference reported between Mild MS and Moderate MS [23]). These analyses indicated that a sample size of 35 would be appropriate for the study design. An additional 5 participants will be recruited to allow for possible dropouts.

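### Four unranked primary outcomes, but the trial is sized on 6MWT distance alone with the full 0.05, and no rule says how the four are read together

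*Protocol article*

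**What the plan says.** The section on primary outcome measures reads: "The primary outcome measures are walking distance, physiological cost index and perceived fatigue and exertion during the 6MWT". The Methods part of the Abstract lists the same four: "Distance walked, perceived exertion, perceived fatigue and the physiological cost of walking (the primary outcome measures) will be compared between the two walking conditions". Neither place ranks them.

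The sample size section uses the singular. Its calculation was for "estimating the sample size required for the primary outcome measure of 6MWT distance", with "power = 0.8; alpha = 0.05", and its rationale is that "a clinically meaningful increase in metres walked by MS patients in this test is 100 m". It prints no standard deviation. It arrives at 35 participants and adds 5 for dropout, making 40.

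The statistical analysis section plans a repeated measures ANOVA of the outcomes, with time and orthosis condition as factors. It gives no order among the primary outcomes, no requirement that all succeed, and no significance level. The 0.05 in the sample size section is the only level in the article.

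The section on the walking protocol defines the physiological cost index (PCI) as the rise in heart rate above rest divided by walk speed.

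**The concern.** Which outcome decides the trial, or how several decide it jointly, is normally fixed in the protocol. Here two sections point different ways. Read from the outcome list, four results carry equal weight. Read from the sample size section, distance carries the full alpha and the only power statement.

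This matters in two ways. First, a claim that the orthosis improved a primary outcome is not held at 5% if any of the four can support it at 0.05. Secondly, a mixed result has no agreed reading. Participants are asked to walk as fast as they comfortably can, so a longer distance with higher exertion is a plausible outcome, and the article does not say whether that would be a success.

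An adjustment introduced later in an analysis plan would not settle it without cost. Splitting alpha across four outcomes would lower the power that the sample size section states for distance.

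**Working it through.** **Inputs from the article.** Four primary outcomes (Abstract; Primary outcome measures). Alpha 0.05, power 0.80, a 100 m difference, a 2x2 cross-over test on differences, N = 35 raised to 40 (Sample size calculations). Sidedness is not stated; two-sided is assumed.

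**1. The plan's own figure.** N = 35 cannot be reproduced because no standard deviation (SD) is printed. Working backwards from the normal approximation, SD of paired differences = 100 × √35 / (1.960 + 0.842) ≈ 211 m. The noncentral t distribution with N − 2 degrees of freedom gives about 205 m. The step from 35 to 40 is consistent with 12.5% dropout: 35 / (1 − 5/40) = 40.

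**2. Chance of at least one false positive.** The conditions are one test of the orthosis effect per outcome, each at 0.05, with any one success counting.

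- Independent tests: 1 − (1 − 0.05)^4 = 1 − 0.8145 = 0.1855.
- Equal correlation between the four tests (assumed values; simulation of two-sided normal tests, 2,000,000 draws):

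| Correlation | At least one false positive |
|---|---|
| 0.3 | 17.4% |
| 0.5 | 15.6% |
| 0.7 | 13.1% |
| 0.9 | 9.3% |

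- Bound with no assumption on dependence: 4 × 0.05 = 20%.

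The article gives no correlations. Some correlation is to be expected, because walk speed, the denominator of PCI, is the distance of the same walk divided by 6 minutes.

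**3. Power for distance if four primaries are kept.** The strictest Holm step is 0.05 / 4 = 0.0125. Take N = 35 as giving exactly 80% at two-sided 0.05, so that the SD is 205 m for a 100 m difference. The noncentrality is 100 × √N / 205.

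- 35 completers: noncentrality about 2.89, power at 0.0125 about 60%.
- 40 completers: noncentrality about 3.09, power about 68%.
- About 51 completers are needed for 80%, which is 11 more than the 40 to be recruited.

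These powers do not depend on the 100 m: with 50 m or 150 m the implied SD scales in proportion and the results are the same.

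**4. Distance as sole primary.** One test at 0.05, so alpha, N and the stated power all stay as printed.

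**The case against.** The strongest reply is that this is a condensed article and its analysis plan is not shown. Multiplicity handling is commonly left to that plan, so its absence here is no error. That is right, and the point does not rest on a missing correction. It rests on what the article does fix: four primaries of equal status, and a sample size that serves one of them with the whole of alpha.

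A reader might infer that the plan tests each outcome at 5% and would claim success on any one. The article says neither. The level is printed only as a sample size input, and the Abstract says only that the outcomes will be compared. The 18.5% is therefore conditional.

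A reader might also take 18.5% as the trial's actual error rate. It is the value for independent tests and is a ceiling only for two-sided, jointly normal tests. With correlated outcomes the rate is probably lower.

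Nor is there a flat contradiction. The singular in the sample size section can be read as the one primary outcome chosen for sizing, which is common practice. That reading is fair, but it still leaves the status of the other three open.

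Finally, exertion is scored repeatedly ("Distance walked and perceived exertion will be recorded each minute") and the fatigue scale is completed "immediately before and after the 6MWT", so one might argue that the choice of value multiplies the tests further. The planned ANOVA has time as a factor and could take in the repeated values, and the summary measure is ordinary analysis-plan detail. The phrase about the walk in the outcome list may qualify exertion alone. These are at most wording points.

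**Conclusion.** The point holds: the article names four unranked primary outcomes, sizes the trial on distance only, and gives no rule for reading the four together. It should be fixed, and cheaply can be, but it does not invalidate the design.

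If each outcome is tested at 0.05 and any one success counts, the chance of a false positive primary result is 18.5% under independence and 17.4% to 13.1% at correlations of 0.3 to 0.7, against a nominal 5%. The correlations are assumed. A rule that all four must succeed would remove this inflation, but the article states none.

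The figures of about 60% and 68% power under a split alpha assume that 35 gives exactly 80% at two-sided 0.05. That cannot be checked: no SD is printed, and 35 is not among the sample sizes entered (20, 30 and 40).

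**What to change.** **Preferred.** Name total 6MWT distance as the single primary outcome at two-sided 0.05, in line with the sample size section. Make PCI, perceived fatigue and perceived exertion key secondary outcomes, tested only after distance succeeds, either in a fixed order or by Holm. Amend the Abstract and the list of primary outcomes to match, and the registry entry if it lists all four.

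N and the stated power for distance do not change, and all data are still collected. The real cost is one of emphasis: the aim in the Abstract puts walking-induced fatigue first, and under this order fatigue and exertion lose primary status and support no confirmatory claim if distance fails.

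**Alternative.** If the sponsor wants all four to remain primary, apply Holm across them and say how mixed results will be read. State the SD used and restate the power for distance. On the assumption above it is about 60% with 35 completers or 68% with 40 at the strictest step; it is higher if other outcomes are rejected first and distance is then tested at a later step.

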### Secondary outcome measures

The secondary outcome measures are hand and foot simple reaction time, choice stepping reaction time, knee extension and ankle dorsiflexion strength, postural sway with feet together and apart and the spatio-temporal, kinematic and kinetic gait parameters.

### Sample size calculations

We used the “Inequality Tests for Two Means in a 2x2 Cross-Over Design using Differences” module from the Power Analysis and Sample Size (PASS) software [18] for estimating the sample size required for the primary outcome measure of 6MWT distance. The following parameters were entered into the calculation: power = 0.8; alpha = 0.05; N(total sample size) = 20,30,40; mean difference between groups at retest = .50,100,150. Standard deviation measures were estimated from previous studies [11]. The difference in 6MWT distance was based on the rationale that a clinically meaningful increase in metres walked by MS patients in this test is 100 m (i.e. the difference reported between Mild MS and Moderate MS [23]). These analyses indicated that a sample size of 35 would be appropriate for the study design. An additional 5 participants will be recruited to allow for possible dropouts.

### Statistical analysis

Initially we will examine the frequency distributions, percentages and calculate means and standard deviations (mean +/−SD) for the outcome measures. Repeated measures analysis of variance (ANOVA) will be used to determine differences in the outcome measures with time and DAO condition as factors. Finally, we will examine associations between 6MWT and measures of fatigue (FSS, MFIS VAS-F & Borg RPE), EDSS scores and Postural Sway data with Pearson correlations. The data will be analysed with the Statistical Package for Social Science (SPSS) software.

We will adjust for other possible confounding variables by using a covariance analysis. Multiple regression analysis will be used to examine significant, independent predictors of 6MWT distance.

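### The planned ANOVA has no clear period (visit) term, although condition order is randomised over two visits and the trial was sized as a 2x2 cross-over

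*Protocol article*

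**What the plan says.** The protocol article describes a randomised cross-over of two walking conditions in 40 participants. Under The walking protocol and Pre- and post-walk assessments, it states: "Following initial screening and assessments, participants will be randomised with respect to condition order". The second visit is then described: "Participants will return to the laboratory within 2 weeks to complete the other 6MWT condition and associated pre- and post-walk assessments". Sample size calculations names the module used for 6MWT distance, "Inequality Tests for Two Means in a 2x2 Cross-Over Design using Differences", and arrives at 35 participants plus 5 for dropout.

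The analysis is given in one sentence of Statistical analysis: "Repeated measures analysis of variance (ANOVA) will be used to determine differences in the outcome measures with time and DAO condition as factors". A later sentence promises a covariance analysis for other possible confounders and names none. Period, visit, order and sequence do not appear in that section.

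**The concern.** In a two-period cross-over every participant supplies one value per visit, so any general difference between visits is part of the data. Here such a difference is plausible for two reasons. The second 6MWT repeats an effort test. The first walk also comes after screening and an initial battery that includes strength, balance and reaction time tests, and no repeat of that battery is described for the second visit.

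If the model has no term for visit, the difference has nowhere to go but the error or the condition effect. With equal orders it inflates the error and power is lost. With unequal orders, part of it is credited to, or taken from, the DAO. The comparison affected is the primary one.

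**Working it through.** **What can time mean?** The article describes three time structures: before and after the walk (VAS-F and the secondary tests), minute of the walk (distance and perceived exertion), and visit.

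- Distance and physiological cost index have no pre-walk value, so pre/post cannot apply to them.
- If time is pre/post or minute, the main effect of condition is a paired comparison of each person's averages, and period is absent.
- If time is visit, each participant fills only two of the four visit-by-condition cells, so a standard two-way repeated-measures ANOVA cannot be fitted. The pre/post contrast that the Background asks for would also be missing.

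No reading gives a usable model with period in it for every outcome.

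**The plan's own figure.** N = 35 cannot be reproduced, because no SD is stated. Working backwards (two-sided alpha 0.05 assumed, power 0.80, t test on N − 2 = 33 df), N = 35 needs effect/SD = 0.488, where SD is that of the within-person difference. That is an SD of 50/0.488 = 102 m for a 50 m effect, or 100/0.488 = 205 m for 100 m.

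**Set-up.** Let D be the within-person difference (DAO minus no DAO), s its SD, π the visit shift (visit 2 minus visit 1), and n1 and n2 the numbers with DAO second and DAO first. The size of π is an assumption throughout.

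*Without a period term:*
- Bias = π(n1 − n2)/N. At 18/17 this is 1/35 = 3% of π; at 20/15, 5/35 = 14%; at 23/12, 11/35 = 31%.
- Variance of D as the analysis sees it ≈ s² + π² when orders are near equal. For π = 0.2s, 0.5s and 1.0s the standard error is inflated by √1.04 = 1.02, √1.25 = 1.12 and √2 = 1.41.

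*With a period term:*
- The estimate is the mean of the two order-specific means of D, with variance (s²/4)(1/n1 + 1/n2).
- Relative to s²/35 this is 1.00 at 18/17, 1.02 at 20/15 and 1.11 at 23/12, whatever π is.

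**Simulation** (N = 35, effect 0.488 SD for power, zero for type I error):

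| Split | Shift π/s | Bias (SD) | Power, no period | Power, period | Type I, no period | Type I, period |
|---|---|---|---|---|---|---|
| 18/17 | 0.2 | 0.01 | 80% | 80% | 4.6% | 5% |
| 18/17 | 0.5 | 0.01 | 75–76% | 80% | 3% | 5% |
| 18/17 | 1.0 | 0.03 | 57% | 80% | 0.7% | 5% |
| 20/15 | 0.2 | 0.03 | 83% | 79% | 5% | 5% |
| 20/15 | 0.5 | 0.07 | 85% | 79% | 4–5% | 5% |
| 20/15 | 1.0 | 0.14 | 80% | 79% | 3% | 5% |
| 23/12 | 0.2 | 0.06 | 88% | 76% | 6% | 5% |
| 23/12 | 0.5 | 0.16 | 94% | 76% | 10% | 5% |
| 23/12 | 1.0 | 0.31 | 97% | 76% | 18% | 5% |

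The higher power without the period term at 20/15 and 23/12 comes from bias that happens to favour the DAO. It is not a gain, and a shift of the opposite sign would work against the DAO.

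**In metres.** At an SD of 102 m, shifts of 0.2, 0.5 and 1.0 SD are about 20, 51 and 102 m. At 205 m they are 41, 102 and 205 m. If the SD were 40 m, a 30 m shift at 18/17 would give power of 70% against 82% for a 20 m effect.

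**How likely is imbalance?** The article states no balancing of orders. Under simple randomisation of 35, the binomial probability of a gap of 5 or more is 50%, and of 11 or more is 9%.

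**The case against.** The strongest reply is that time is undefined rather than wrongly defined, and that a condensed article may leave the model's details to a fuller document. This stands in part: the defect is an unclear factor, not a proven refusal to model period. But the article does fix the factors it will use, and none of the readings of time supplies period in a fittable model. The covariance sentence does not rescue it either: visit varies within person and is not named.

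A reader might infer that the design builds in a visit effect. The documents do not go that far. They give an order of events, not a same-day schedule for screening and the first walk; the Abstract's description would allow a separate screening visit; and no size or direction is stated. The repeat of an effort test makes a visit effect plausible, no more.

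A reader might also infer that the stated analysis inflates type I error in general. It does not. At 20/15 the error rate does not exceed 5%, and averaged over simple randomisation it is 4.7 to 5.1% at every shift examined. The bias likewise averages to zero over a fair randomisation; it is conditional on the split that occurs.

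Nor is the handling of dropouts a strong argument. The 5 extra participants are recruited so that 35 remain, and nothing says that those who drop out would supply one usable walk.

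**Conclusion.** The point holds as a recommendation: the stated model does not match the stated cross-over, and naming a period term is a specific and nearly free improvement to the primary comparison. Its size depends on a visit shift and an SD that the article does not give. With near-equal orders the loss is negligible at 0.2 to 0.3 SD (power 79 to 80%), modest at 0.5 SD and serious only near 1.0 SD, which at the SD implied for a 50 m effect is about as large as the 100 m the plan calls clinically meaningful. Conditional bias matters if the orders turn out clearly unequal. Reading this as a fault that invalidates the trial's type I error would overstate it, since that needs both a visit shift and a split of the order of 23/12.

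**What to change.** Define time separately for each outcome, and add period (visit 1 or 2) as a fixed effect.

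- **6MWT distance and physiological cost index:** condition and period as fixed effects with a random participant effect, for example in a linear mixed model. The complete-case equivalent is to compare within-person differences between the two orders.
- **VAS-F, strength, reaction time, balance and gait:** keep the pre/post factor and its interaction with condition, and add period. Replacing the ANOVA with a model of condition and period alone would remove the contrast these outcomes were measured for.
- **Sequence:** optional. It mainly helps to examine carry-over; period is the term that restores precision and removes the conditional bias.

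Report the condition effect with its 95% confidence interval. The cost is a change of wording and one degree of freedom. No new data are needed, because visit and order follow from the conduct of the trial, and N = 35 need not change if the orders are kept near equal.
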